#### Subject withdrawals

After enrolment subjects are free to withdraw from the study at any time. In addition, the principal investigator and/or site investigator may decide to withdraw a subject if a protocol violation is suspected. The date and reasons for the withdrawal will be clearly stated in the subject’s case report form. No subjects will be withdrawn for not attending scheduled visits or calls during the fieldwork periods or timepoint, provided they can be contacted later and can provide a reason for non-attendance. Otherwise, they will be entered into the lost-to-follow-up process. Withdrawn subjects will not be replaced.

### Fieldwork periods

Fieldwork periods will cover the first 12 days of every timepoint (Figure 1). Subjects will visit the study centres three times during these 12 days (visits 1, 2 and 3), on days 1, 9 and 12. Day 1 of the first fieldwork visit will be used to assess the eligibility of subjects according to the inclusion and exclusion criteria and to assign each subject with a unique study code. The subjects’ identification and study codes will be checked at each visit.

During visit 1, medical history and demographic data will be updated, and blood pressure, spirometry, weight, height and ECG (latter two, first fieldwork period only) will be assessed. Subjects will be given aluminium containers for daily collection of cigarette butts from all cigarettes smoked on days 2–9 and instructed verbally how to collect them. Interviewer-led questionnaires on smoking behaviour will be completed.

During visit 2, the butts from days 2–8 will be counted to calculate average daily consumption and cigarette brands will be checked. Aluminium containers will be supplied for collection of cigarette butts on day 10, along with a filter cutter/collector, and instructions for the collection of part-filters for filter analysis from cigarettes smoked on day 11. Polyethylene containers, also for use on day 11, will be provided with verbal and written instructions for 24 h urine collection along with a report sheet on which to record any medications taken during this period. A 1-day supply of the subjects’ current cigarettes will be provided for smoking on day 11. A sensory evaluation questionnaire will be provided for self-completion during day 11.

During visit 3, the used cigarette butts collected on days 9 and 10, the 24 h urine sample and cigarette part-filter samples from day 11 and the self-completed sensory questionnaires will be collected. Saliva samples will be taken under the supervision of a study nurse, for analysis of the nicotine metabolites cotinine and *trans*-3′-hydroxycotinine (OH-cotinine). A self-reported questionnaire on recent life changes and interviewer-led questionnaires on smoking behaviour and quality of life will be completed.

Study staff will also contact participants by telephone four times during each timepoint, at approximately 2 and 4 months after the last fieldwork visit (calls 1 and 2), 1 week before the next fieldwork period (call 3) and on day 10 of fieldwork periods (call 4). During telephone contact, the following activities will take place: calls 1 and 2 will be interviews with subjects to verify they still meet the original non-medical inclusion criteria and to record which cigarette products are currently being smoked, reasons for any change in current cigarette product smoked since the previous timepoint and self-reported daily consumption; call 3 will be to remind subjects of their visit 1 appointment and determine whether they have changed their cigarette product; call 4 will be to remind subjects to collect part-filter tips and urine on day 11.

### Study procedures

#### ECG assessment

During visit 1 of the first fieldwork period only, subjects will undergo 12-lead resting ECG with a 10 s rhythm. Subjects will be supine for at least 5 min before the test. The ECG will be performed, documented and assessed by a physician. Any subject with an abnormal rhythm or trace shape on ECG will be excluded from the study and advised to consult a cardiologist. ECGs may be undertaken in other fieldwork periods if a subject reports relevant symptoms, but he or she will be advised to consult a cardiologist and a copy of any follow up report will be retained.

#### Blood pressure and pulse rate assessments

Supine blood pressure and pulse rate will be measured during visit 1 of the first fieldwork visit. Subjects will be supine for at least 5 min before assessments. During visit 1 of all subsequent fieldwork periods, blood pressure and pulse rate measurements will be taken with subjects in the sitting position. Blood pressure assessment will also be performed at other times if judged to be clinically appropriate by the study staff.

#### Spirometry

Spirometry will be used to measure forced expiratory volume in 1 s (FEV_1_) as evidence of changes in pulmonary function during the course of the study. Lung-function tests will be performed at visit 1 of all fieldwork periods. All subjects will stand during lung-function measurements and the best of three technically acceptable attempts will be taken as the true measure of lung function for each timepoint. At least one other attempt must give a result within 5% of the best value for the average to be valid. If necessary, measurements will be repeated until two attempts within 5% of each other are obtained. If a subject shows signs of fatigue, testing will be halted and will only recommence at the physician’s discretion.

#### Cigarette butt collection

In every fieldwork period, subjects will be provided with labelled aluminium containers, and instructed to collect butts from all cigarettes smoked on days 2–9 in those aluminium containers provided at visit 1, and the butts from cigarettes smoked on day 10 in the containers provided at visit 2.

During visit 2, the collected cigarette butts from days 2–8 will be counted at the study centres to calculate average daily cigarette consumption and identify the brands smoked, where possible. After counting, the butts will be discarded. Subjects who have deviated from their normal cigarette consumption (defined as an increase or decrease in consumption on ≥1 day by more than 25% of the average daily consumption from days 2–8) will complete an interviewer-led questionnaire to identify the reasons for the deviation. At visit 3, the collected butts for days 9 and 10 will be counted in the same manner.

#### Smoking and part-filter collection

On all days during the study, except day 11 of the fieldwork periods, subjects will purchase and smoke their own cigarettes. On day 9 of every fieldwork period, cigarettes that match each smoker’s current product will be provided in sufficient quantity to match average daily consumption, along with a labelled filter cutter with integrated collection tin. The subjects will be requested to smoke only these cigarettes on day 11, from the first to the final cigarette of the day, and to use no other nicotine-containing products during this 24 h period. Subjects will be instructed to smoke the provided cigarettes as usual and to cut off and collect 10 mm mouth end sections of the filter tips from every cigarette smoked that day. To minimise the possible influence of changes in smoking behaviour caused by social circumstances and environment, fieldwork periods will be scheduled to ensure that the collection of filter tips will occur only on working days. The number of filter tips in the filter cutter will be counted on day 12.

Filter tips must meet the quality guidelines of the sponsor (i.e. not crushed or containing ash and of approximate correct length). If they are not of adequate quality, subjects will collect them again on the next available working day, along with repeating the 24 h urine collection. The collected cigarette filters will be stored at room temperature pending dispatch to the sponsor for analysis of tar and nicotine content. These data will be compared with calibration curves from a range of machine smoking regimes, where the nicotine and tar yields and filter nicotine and tar contents are known and the MLE to nicotine and tar per cigarette calculated [21]. Daily MLE estimates will be calculated by multiplying the per-cigarette values by the number of cigarettes consumed on day 11 of the fieldwork periods.

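### Day-11 cigarettes are issued to match the subject's average and only these are to be smoked, so the day-11 count, and daily mouth-level exposure through that count, are biased downwards

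*Protocol article*

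**What the plan says.** The procedure is in the protocol article under Smoking and part-filter collection. On day 9, cigarettes of the subject's current product "will be provided in sufficient quantity to match average daily consumption". The restriction follows: "The subjects will be requested to smoke only these cigarettes on day 11, from the first to the final cigarette of the day", with no other nicotine-containing product during the 24 h. The next instruction is: "Subjects will be instructed to smoke the provided cigarettes as usual". Daily MLE to tar and nicotine is then obtained by "multiplying the per-cigarette values by the number of cigarettes consumed on day 11 of the fieldwork periods".

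Fieldwork periods describes the same issue of cigarettes: "A 1-day supply of the subjects’ current cigarettes will be provided for smoking on day 11". It also shows where the average comes from: at visit 2, "the butts from days 2–8 will be counted to calculate average daily consumption". These butts are from the subject's own cigarettes, smoked before any are issued.

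Neither section mentions a surplus, a rounding rule, or what happens if the supply runs out. Under Urine collection and processing, the 24 h collection covers day 11 up to the first void on day 12.

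**The concern.** Taken as written, the rule constrains the count on one side only. A subject whose natural day-11 smoking would be below average is free to smoke less. A subject whose natural smoking would be above average runs out. Averaged over subjects, the count must fall below natural smoking whenever the limit binds for anyone, and the error passes into daily MLE as a factor.

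This works against the protocol's own aim for day 11. Subjects are told to smoke normally, and collection is confined to working days to limit outside influence on behaviour. MLE is among the main measures in Study objectives, and the Background lists number of cigarettes among the routes of compensation. A supply fixed at the average leaves no room for a high day. Under Cigarette butt collection, the protocol provides for such days, with a questionnaire for "an increase or decrease in consumption on ≥1 day by more than 25% of the average daily consumption".

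**Working it through.** The documents state no day-11 count, supply surplus or day-to-day standard deviation, so there is no figure of the plan's own to reproduce. The size has to be shown over an assumed range.

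**Inputs from the protocol.** The supply matches average daily consumption. That average is taken here to be the mean of the seven daily butt counts for days 2–8, because it is counted at the visit where the cigarettes are issued. Day 11 is always a working day. Days 2–8 are seven consecutive days and so always include a weekend. Entry requires at least eight cigarettes per day.

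**Assumptions, not in the protocol.** Subjects comply fully. Daily counts are roughly normal, with a within-subject CV of 10%, 20% or 30%. Mean consumption is 8, 15 or 20 per day.

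**Formula.** Let X be the free day-11 count, with mean μ and SD σ, and M the mean of the seven earlier days, with SD σ/√7. The count under the limit is min(X, M) = X − max(X − M, 0). With equal means, X − M has SD σ√(1 + 1/7) = σ√(8/7) = 1.069σ. The expected loss is therefore

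0.399 × 1.069 × σ = 0.426σ, or 0.426 × CV as a fraction of the mean.

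For a subject on 15 per day with CV 20%, σ = 3. The loss is 0.426 × 3 = 1.28 cigarettes, and 1.28/15 = 8.5%.

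**Results.** The first results column is the formula. The others are simulations with integer counts (200,000 subjects per setting).

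| CV | Shortfall, supply = 7-day mean | Days on which the limit binds (supply rounded to nearest) | Shortfall, supply rounded up | Shortfall, rounded up, 15 per day, weekend smoking 10–30% higher |
|---|---|---|---|---|
| 10% | 4.3% | 28–41% | 2.4–3.3% | 0.8–2.0% |
| 20% | 8.5% | 39–45% | 6.1–7.5% | 4.0–6.0% |
| 30% | 12.8% | 42–47% | 10.3–11.7% | 7.9–10.1% |

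Ranges in the third and fourth columns run over means of 8 to 20 per day. In the last column they run over the assumed weekend excess, which puts the seven-day mean above the working-day mean and so loosens the limit. If weekend smoking were lower than on working days, the limit would tighten instead.

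**Consequence for daily MLE.** With per-cigarette MLE unchanged, daily MLE falls by the same percentage as the count.

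**Consequence for group comparisons.** With the same CV in two groups, both means are multiplied by the same factor and their ratio is unchanged. If one group had CV 10% and another 20%, the ratio would be off by (1 − 0.043)/(1 − 0.085) = 0.957/0.915 = 1.046, about 5%. The protocol gives no reason to expect either case.

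**The case against.** The strongest reply is that a hard limit is inferred. The quantity is described as sufficient, which could mean at least enough. The restriction is a request, and tips are collected from every cigarette smoked that day. Pack rounding and spares are details that an article leaves to the full protocol. Part of this stands: the limit is not absolute, and generous supply at the sites would shrink the effect. But the two stated rules, a quantity matched to the average and only these cigarettes, produce the one-sided constraint when followed. The point therefore rests on what is stated.

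A reader might infer more than the documents support:

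- **That daily MLE and the urine biomarkers are themselves capped at the average.** Only the number of cigarettes is limited. Per-cigarette MLE is free and may rise when cigarettes run short. Urine is affected only through the number smoked, and the documents give no way to size that.
- **That a shortfall of around 10% uses up half of the 20% biomarker difference in Sample size and power calculations.** That 20% is a difference between groups in a biomarker. The shortfall is a shift in a count that all groups share, so the two are not comparable.
- **That the protocol predicts frequent days more than 25% from the average.** That figure is only a trigger for a questionnaire. It gives no frequency, SD or CV.
- **That compensation through number of cigarettes is hidden.** Average consumption comes from days 2–8 and is untouched. The supply follows the current average at each fieldwork period, so a lasting change after switching still shows.

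**Conclusion.** The concern holds for the day-11 count and, through it, for the absolute level of daily MLE. Under full compliance, with supply equal to the seven-day mean and an assumed CV of 10–30%, the mean count is about 4–13% too low. With supply rounded up and weekend smoking assumed 10–30% higher than on working days, the figure at 15 per day is about 1–10%. The direction is firm whenever the limit binds; the size depends on the assumed CV, on compliance and on how sites set the supply.

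For relative comparisons between groups the bias largely cancels if within-subject variability is similar. It would not cancel if variability differed by group or over time, but nothing in the protocol shows that it does. Any effect on 24 h urine measures is possible but cannot be quantified. This is a worthwhile, inexpensive improvement and does not undermine the study's main comparisons.

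**What to change.** Add to Smoking and part-filter collection, and to the subjects' instruction sheet, that the number issued is not a limit on day-11 smoking. If it runs out, any further cigarettes of the same product are recorded, and their tips are cut and collected with the rest.

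Keep the day-11 count as the main multiplier for daily MLE, and add a sensitivity analysis that uses the days 2–8 average. That average should not replace the day-11 count: it mixes weekend smoking into a working-day measure, breaks the same-day match with the urine collection, and does nothing for the urine measures.

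The cost is wording only. Tips are already counted on day 12 and butts from days 2–8 are already counted at visit 2, so no visit or assay is added. The downside is that a few non-issued cigarettes of the same product enter the filter analysis; recording their number keeps this visible.

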#### Urine collection and processing

Urine will be collected into standard-weight polyethylene containers. The 24 h collection period will always be on working days to minimise the possible influences of social circumstances and environment on smoking behaviour. The collection period will commence after the first morning void, which will be discarded, and will continue throughout day 11 and include the first morning void on day 12. The times of the first void, first collection and last collection will be recorded by subjects on the provided report sheets. During each 24 h collection period, the containers will be stored in a cool bag with two frozen cooling elements.

Subjects will document on the provided report sheets any medications taken during the 24 h urine collection period. The bulk urine for each subject will be frozen within 15 min of receipt and transported to the CRO, where it will be stored at approximately –20°C until analysis, when it will be thawed and the weight recorded. A nominal value for specific gravity (1.018) will be used to calculate urine volume [22].

After the bulk urine has completely thawed, aliquots will be transferred into suitably labelled polypropylene tubes and stored at approximately –20°C pending dispatch for analysis by ABF GmbH, Munich, Germany, and long-term storage at Covance, Leeds, UK.

Urine samples will be analysed for the concentration of nicotine and five main metabolites (cotinine, OH-cotinine, nicotine-*N*-glucuronide, cotinine-*N*-glucuronide and *trans*-3′-hydroxycotinine-*O*-glucuronide) and the metabolites of NNK, 4-(methylnitrosamino)-1-(3-pyridyl)-1-butanol (NNAL) and NNAL-glucuronides (total NNAL). Creatinine concentration will be determined to provide an indication of urine collection compliance.

#### Saliva collection

On visit 3 of each fieldwork period, saliva samples will be collected after 15:00 h from all subjects, for measurement of the nicotine metabolites cotinine and OH-cotinine. Samples will be collected with Salivettes (Sarstedt, Nuembrecht, Germany). Subjects will be asked to place a cotton wool swab in their mouth and move the swab with a slight chewing action to allow for saturation with saliva over a 2 min period. Within 15 min of collection the samples will be frozen and stored at approximately –20°C, pending dispatch for analysis.

#### Monitoring of changes in cigarette consumption

Checks on whether each smoker has changed their main cigarette product will be carried out at calls 1, 2 and 3 of each timepoint. The products reported by the subjects during call 2 will be obtained by the sponsor for supply at the next fieldwork period. Call 3 will identify any changes in a subject’s cigarette product smoked, one week before the fieldwork period. Change to cigarettes with a lower ISO tar yield compared to those smoked at baseline (e.g. from 10 mg to 6 mg), a higher ISO tar yield (e.g. from 6 mg to 10 mg) and to a different cigarette with the same ISO tar yield (e.g. one 10 mg ISO tar product to another 10 mg ISO tar product) will be permitted. Subjects will be considered no longer eligible if they change their smoking habits in any of the following ways: change to smoking cigarettes that are not TVO compliant; change to smoking non-filtered products; change to smoking self-rolled (roll your own) cigarettes or self-filled “stix” (make your own) cigarettes, with or without filters; change to using chewing tobacco or other smokeless tobacco products; and use of nicotine-replacement therapy or decision to quit smoking.

The MRA will maintain all information regarding switches in products and smoking behaviour.

#### Completion of questionnaires

On day 1 of visit 1 of every fieldwork period, subjects will complete an interviewer-led electronic questionnaire on smoking behaviour, including the Fagerström Test for Nicotine Dependence [23]. Questionnaires about deviation from normal cigarette consumption will be completed during visit 2 of fieldwork periods, on day 9, and questionnaires on sensory attributes will be provided for self-completion at home on day 11. These will be returned on day 12 at visit 3. During visit 3, subjects will also be required to self-complete the Recent Life Changes questionnaire [24] and the interviewer-led SF-36v2 Quality of Life questionnaire [25]. The responses to the self-completed questionnaires will be entered into an electronic data capture system at the study centres by study personnel.

#### Lost to follow-up

Subjects will be permitted to miss whole timepoints provided they are contactable and can give valid reasons for doing so. Subjects who cannot be contacted during scheduled events (visits or calls) will enter the “lost-to-follow-up” process. The process starts with a telephone call, followed up by a second call two weeks later, if the subject makes no response. If there is still no response from the subject, he or she will be sent a letter by fax or e-mail if contact information is available. The final step in this process is that a registered letter will be sent to the subject. If the subject responds to any contact, the process will be stopped. Otherwise, the subject will be withdrawn from the study by the principal investigator.

### Sample size and power calculations

It is expected that the subjects will separate into three groups during the study: subjects who do not change product from the original 10 mg ISO tar product throughout the study; those who change to cigarettes with ISO tar yields of 7 mg or lower (down-switchers); and those who change to cigarettes with ISO tar yields of 8–10 mg (side-switchers). A fourth group is possible that will include subjects who down-switch but subsequently change back to cigarettes of higher tar yields (up-switchers). Subjects cannot up-switch from the original 10 mg ISO tar product due to the upper limit of 10 mg ISO tar for cigarettes sold in the EU [14]. Analysis of biomarkers of exposure in sub-populations of smokers and non-smokers in Germany indicated that differences of 20% between the subject groups for each respective biomarker would yield results significant at an alpha level of 0.05 where group sizes were greater than n = 50 [26]. Power and sample size calculations were also used to determine thresholds required to detect significant differences between subject groups. These calculations showed that to achieve a power of 80%, a sample size of 51 will be required to detect differences of 2 mg in MLE to tar between subject groups [26]. To achieve a minimum of 51 subjects in each of the three subject groups over multiple timepoints and taking account of predicted product switching rates (3.7% down-switching and 10% side-switching), and allowing for an annual reduction of 20.4% (based on a combination of subject withdrawal and attrition from the study and an annual quitting smoking rate of 12.4%), it will be necessary to recruit 1000 subjects. Based on the predicted annual reduction of 20.4%, it is predicted that 319 subjects will complete the study.

### Statistical analysis

The statistical analyses to address the primary and secondary objectives will be performed on the final per protocol population. Data will be tested for normality and homogeneity of the variance and, if appropriate, data will be transformed to try to satisfy analysis of variance (ANOVA) assumptions. If normality approximation cannot be achieved, non-parametric methods may be employed. A linear mixed model will be used to assess group changes over time for all MLE, biomarkers of exposure and consumption measurements. The model will include fixed effects due to subject group (non-switcher, down-switcher or side-switcher), timepoint, gender, subject group*timepoint interaction and age as a covariate. The interaction term will be removed from the model if not statistically significant. Data from the first timepoint will be used to account for possible subject differences at the start of the study. Repeated measures ANOVA will be performed to account for the correlation over time within each subject.

Established procedures will be used to determine the extent of any compensation effect, as a result of subjects switching products. These procedures calculate compensation indices on the basis of machine-smoked yields and exposure data [13,27].

A detailed statistical analysis plan of the methodology to be used will be prepared before the database closure.

